
### Research methods, measuring instruments and procedures

#### Organizations to guide the implementation process (question 1)

First we will explore which care, welfare and other organizations involved in dementia care in the participating countries should be engaged in the implementation process of the Meeting Centers Support Program. The project team in each country, consisting of the academic partner and other partner research organization(s), a care organization and a welfare organization and a representative of the national or regional Alzheimer association, will 1) analyze the relevant care, welfare and other organizations and associations in the region/country; and 2) compile a list of potential partner organizations interested in the implementation of the MCSP, based on discussions with their representatives. All these organizations will be invited to an information meeting at which the MCSP and the aims and methodology of the implementation project are explained and people are invited to join the initiative group to set up a meeting center.

#### Identifying facilitators and barriers of implementation (question 2)

In previous research on successful implementation of MCSP in the Netherlands [22], a theoretical model for adaptive implementation was developed to inventory facilitators and barriers of implementation of MCSP [16, 17]. This model describes influencing factors on different levels of implementation, e.g. on a micro (primary process), meso (cooperation between organizations) and macro level (laws and regulations), and during different phases of the implementation process (preparation, execution, continuation).

Based on the results of this study, a questionnaire will be composed on potential facilitators and barriers, and translated in languages of the three countries. This questionnaire will also record characteristics of the innovation itself, i.e. the Meeting Centers Support Program, and other preconditions that can have a facilitating or impeding influence during the implementation process (preparation phase, execution phase, continuation phase) will be included.

This questionnaire will be discussed with organizations that agreed to take part in the initiative group. They will be asked to indicate which facilitators and barriers they foresee to influence the implementation of MCSP in their own country, as well as to describe additional expected facilitators and barriers that are not included in the checklist yet. The results will be discussed in the initiative groups, summarized per country and disseminated to all participating countries. Subsequently, the list of foreseen facilitators and barriers will be used by each initiative group to define promising implementation strategies. In each country the results will be summarized for each phase and level of implementation. This document will be sent to all participating countries and will inform the development of a detailed implementation plan in each country.

During the implementation phase a process analysis will be conducted for which quantitative and qualitative research methods will be used. In each participating country data will be collected from key figures in the implementation process, who are selected by means of ‘purposive sampling’ [23]. The following criteria will be used: representatives from different organizations (care and welfare) involved in the implementation of the MCSP, key figures with professional and financial expertise, and key figures at the local level (municipality) and at the regional/national level (e.g. Alzheimer association). Different types of key figures will be asked a selection of questions, depending on their area of expertise and involvement in the implementation process. Data will also be drawn from the minutes and reports of the initiative groups in the different countries to inform an inventory of facilitators and barriers to implementation.

##### Country specific implementation plans (question 3)

Based on the results of the inventory of (potential) facilitators and barriers for implementation of the MCSP and the proposed implementation strategies in each country, a country specific implementation plan will be developed by each initiative group to guide a successful implementation of the MCSP. The initiative group will be led by one of the partner organizations (to decide per country/region who takes the lead: a research center, care or welfare organization or Alzheimer association). The process to create the implementation plan will consist of several steps/tasks that need to be completed before the actual implementation can take place. This process takes approximately 1 year. The steps/tasks will include: definition of the target population (inclusion and exclusion criteria), content of the support program, requirements of the location and listing of locations that meet these requirements, cultural issues that are relevant to consider for the implementation (such as what is the cultural norm for dementia care?), number and educational background of personnel and required training, funding of the MCSP, collaboration with other organizations, and development of a communication plan in order to communicate the existence of the MCSP as a resource of support for persons with dementia and carers to appropriate stakeholders (e.g. health care professionals, volunteer associations for dementia, local social care workers, responsible local government, etc.). The initiative groups in each country will form subgroups to elaborate on the various steps/tasks in the action plan. The progress made in the subgroups will be discussed within the monthly plenary initiative group meetings.

Also, implementation materials will be developed, taking into account the regional context, that can support the provision of information about the MCSP among various target populations and create interest in the MCSP. Existing materials developed in the Netherlands will be adapted and translated as necessary. Implementation and dissemination materials that are already available in the Netherlands are: a DVD on the MCSP (also available in English), a flyer on the MCSP, a practical implementation guide [24], a course for personnel of the Meeting centers, scientific and professional publications (in English) on the effectiveness and implementation of the MCSP in the Netherlands, a website with information on the Meeting centers in the Netherlands, a Dutch LinkedIn group for people interested in or working in meeting centers.

#### Evaluation of (cost)effectiveness (question 4a)

To determine the severity of the dementia the Reisberg’s Global Deterioration Scale [25] will be used. Background information will be collected for all participants, including socio-economic status, gender and comorbidities, as well as who referred them to the MCSP/usual care, in order to identify the characteristics of the (groups of) people with dementia and carers who use the MCSP and the usual care and to learn more about the pathways to care in the different countries.

The selection of the outcome measures was based on the Adaptation-Coping model (cognitive, emotional and social adaptation) [20] and previous research into the effectiveness of MCSP on behavior, mood and quality of life of people with dementia and general health, caregiver distress, sense of competence of the carers [12, 13].

For the person with dementia the NeuroPsychiatric Inventory (NPI) [26], the Cornell scale for depression in dementia [27], Duke social support inventory [28], Stigma Impact Scale: Neurological Impairment [29], the subscale self-esteem of the Dementia Quality of Life questionnaire (DQOL) [30], and the Quality of Life-Alzheimer’s Disease Scale (QOL-AD [31] will be used. For the carers the UCLA Loneliness scale [32], General Health Questionnaire-12 [33], NPI-caregiver distress scale [26], and the Short Sense of Competence Scale (SSCQ) [34] will be used as an outcome measure. Data collection on all outcome measures will occur at baseline and after 6 months of support.

For evaluation of the cost-effectiveness, data will be collected on: service use (incl meeting center services used by person with dementia and carer), psychotropic medication, admissions into a hospital and into a long term care setting (incl. temporary admission as respite for the carer), carer time spent on caring. For this data collection specific questionnaires will be administered from the carers at Month 0 and 7. In addition, cost diaries are filled in by the carers during the whole intervention period.

#### User evaluation (question 4b)

In order to assess the opinions of the people with dementia and their carers on the support they receive, and on the various elements in the support program, all new participants in the support program who agree to take part in the study will be interviewed in-depth, after 3 and 6 months of participation. The interview will utilize a questionnaire about the different program elements. The people with dementia will be interviewed by an independent interviewer, the carer will receive a written questionnaire and will be asked to complete it and to send it directly to the research team. The two questionnaires that were developed for this user evaluation among people with dementia and their carers in the Netherlands [12] will be translated in the native languages of the participating countries.

A qualitative evaluation will also be undertaken in each meeting center by means of separate focus groups for people with dementia and carers (a total of 2 focus groups per MCSP) to explore their experiences with the MCSP. The focus groups will be recorded and transcribed.

#### Dissemination strategies (question 5)

In collaboration with the care and welfare organizations, Alzheimer organizations, members of the initiative groups and other relevant stakeholders in the participating countries, the project team in each country will develop a country specific plan to disseminate the project results and stimulate further dissemination and implementation of MCSP in these countries. An international dissemination plan will also be developed, including a project website to raise (inter)national awareness of the proposed project and to disseminate the emerging findings, publications in scientific and professional journals, the newsletters of the national Alzheimer organizations and Alzheimer Europe, and presentations on conferences for scientists, professionals and the general public. In addition a practical implementation guide and toolkit will be developed.

During the project period a network of interest will be established by creating and updating a database with contact details of stakeholders who have interest in the MCSP in the participating and other EU countries. This network will be informed on the progress of the project by means of an e-newsletter, including details of the training courses and the developed implementation materials.

At the end of the project, in each country a final national/regional event will be organized to present the findings of the implementation study to relevant stakeholders, such as (in)formal carers, care and welfare organizations, policy makers, local government, health insurers and charity.

### Overall project structure and time plan

The two project phases (1: Exploration and preparation; 2: Implementation and evaluation) will be carried out in 18 months each (total 36 month). The work is divided into seven workpackages (WPs; see Fig. 1):
*Project management (Month 1‑36):* Internal and external project management, ensuring that the project’s main objectives are realized on schedule and according to budget.
*Exploration, mapping and recruitment of organisations (Month 1‑3):* care and welfare organisations providing dementia care in each country will be invited for the initiative group; this initiative group will provide the information needed in WP 3, 4 and 5.
*Identification of conditions for implementation of MCSP in participating countries (Month 3‑6):* Based on the results of the Dutch implementation study [16] *foreseen* facilitators and barriers will be inventoried by the initiative groups in each country. Promising solutions and implementation strategies will be described. This will be input for WP 4.
*Preparation of implementation strategies and materials (Month 7‑17):* The country specific implementation plans will be prepared. Already existing Dutch implementation strategies and materials will be used and adapted, if necessary. This will be input for WP 5.
*Implementation of MCSP (Month 16‑36):* A course is developed and offered to the personnel of the meeting centers. In addition, the pioneer workshops are provided for organizations who are interested to set up a meeting center in their own region. In each participating country the MCSP is adaptively implemented in at least one region, in one meeting center.
*Evaluation of implementation (Month 19‑36):* The efficacy and cost-effectiveness of the implementation of the MCSP, the satisfaction of the participants (people with dementia and carers) and the implementation process will be evaluated in at least one region per country.
*Dissemination of project results (Month 1‑36):* The results on implementation of the MCSP will be disseminated in the participating countries, in Europe, and worldwide, based on (inter)national dissemination plans. A database on interested stakeholders will be created to form the network of interest.

**Fig. 1 Fig1:**
[figure not shown]
Structure of MEETINGDEM project: Workpackages and interrelationships

### Analysis

#### Process evaluation (question 2)

The data on facilitators and barriers of implementation, collected in the different implementation phases by the developed checklist, will be analyzed descriptively for each phase and level (micro, meso, macro), and for each country and overall (international). In addition, differences between countries will be analyzed. Finally, a comparison will be made with the results from the previous study into the implementation of MCSP in the Netherlands.

The written material obtained from the minutes and reports of the initiative groups meetings in the different countries will be analyzed qualitatively on mentioned facilitators and barriers of implementation during the preparation phase. The material will be read and coded by two independent researchers who will assign key words to extracts of the text. Codes will be assigned based on the checklist of possible facilitating and impeding factors (deductive method). New codes will be added if necessary (inductive method). In case of disagreement, the assessors will discuss the coding in detail until consensus is reached. After that all coded texts will be arranged by theme and summarized for each country and compared with each other. The main similarities and differences between the countries will be summarized. To aid the qualitative analysis a computer program will be used.

#### Evaluation of effectiveness and cost-effectiveness (question 4a)

The baseline characteristics of participants in the MCSP group and control group will be analyzed descriptively and differences between the groups will be tested (two-sided, alpha 0.05) by t-tests and Chi2 tests, depending on the type of data (ordinal, nominal). The data collected on the outcome measures will be analyzed by covariance analyses (ANCOVA’s) on the posttest measurements including the baseline measurements as covariates in the analysis. In addition, potential confounding variables will be included as covariates, i.e. characteristics that differ between the groups at baseline and are correlated with one or more outcome measures. For each outcome measure the effect size will be calculated according to Cohen (1977; small effect d = 0.2; moderate effect d = 0.5; large effect d > 0.8).

The cost-effectiveness analysis will compare the outcomes and costs of the MCSP at the 7 month follow-up (a) from a health and social care perspective, and (b) from a societal perspective (including unpaid carer costs). Cost-effectiveness outcome measure will be: Incremental cost per quality-adjusted life year (QALY), using self-reported EuroQol EQ-5D-5 L [35].

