To answer *research question 4* the implementation of the MCSP will be evaluated (in each country and overall) regarding:(cost)effectiveness of the MCSP on behavior, mood, social support, experienced stigma and quality of life of people with dementia and loneliness, general health and sense of competence of their carers and delay of institutionalization, by means of a controlled trial (pre-test and post-test control group design) with measurements at Month 0 and Month 7, in which the MCSP will be compared with usual care in each country. This timing of measurements was chosen in line with the design of the previous research into the MCSP in the Netherlands to make comparison possible. The aim is to recruit people with mild to moderately severe dementia (Global Deterioration Scale score 4 and 5; mild to moderate dementia) and their carers, as these are the target group of the MCSP. There will be no restrictions on the age of people with dementia or carers participating in the program. In total 75 patient-carer dyads who will be offered the MCSP and 75 patient-carer dyads usual care. This number of dyads is based on a power analysis: in case of moderate effects (d = 0,5), a power of 0.80 and alpha 0.05, at least 64 dyads are needed. Taking into account a drop-out of 15% 75 dyads need to be recruited (25 per country). To check for comparability of the MCSP group and the control group (per country and overall), in each country at baseline the groups will be compared on the following characteristics: severity of the dementia and degree of assistance/care needed by the patient, and the sense of competence of the caregiver. During the intervention period possible longitudinal changes in the person with dementia will be monitored (illness, physical disability, medication and the use of other types of support than offered in the experimental or the control group). Reasons for drop out, and special (life) events in the period of 1 month before the measurements will also be checked. To compare the costs of the two conditions the following costs will be taken into account: service use, use of psychotropic medication, hospital admission and admission into a long term care setting (incl. temporary admission as respite for carer);user satisfaction among people with dementia and carers participating in the program by means of a survey and focus groups;

To answer *research question 5*, national and international dissemination plans will be developed.

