Because the (cost)effectiveness study is conducted within an implementation study this may entail the following risks: the MCSP is not yet fully implemented during the experimental period or the personnel does not yet fully work according to the vision and principles of MCSP. This will decrease the effectiveness of the intervention, and may lead to recruitment problems in the starting period. If the first meeting centers in the three countries do not reach the number of participants required according to the power analysis (25 per country, taking into account an expected drop-out rate of 15%), more meeting centres are needed to be included in the study. This may be difficult due to funding and finding suitable locations. To minimize these risks a long preparation period of 12 months is planned, before the actual start of the centers. This will give the initiative groups enough time to prepare the implementation, arrange the necessary funding and location(s), communicate the new service offer to public and care and welfare providers in the region, recruit participants and train the personnel. Also during the first year of implementation, recruitment of participants will be continued (9 months) and, as a follow-up of the training, the personnel will receive supervision and guidance from one of the trainers and trained project leader in each country (five group supervision meetings).

Though country specific implementation plans will be created, the three meeting centres may encounter different barriers to implementation (such as difference in staff competencies and collaboration with other care partners), which can have an effect on the care received by people with dementia and their informal caregivers. A clear description of the adaptive implementation of MCSP in practice will help to identify these differences and if necessary, take these into account in the effect analyses.

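### The pooled ANCOVA fixes no country term, and the stated 0.80 power and 5% error hold beyond the participating centres only if outcomes do not vary between centres

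*Protocol article*

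**What the plan says.** **Sample size** (Protocol article, Phase 2: implementation, evaluation and dissemination). The basis is "in case of moderate effects (d = 0,5), a power of 0.80 and alpha 0.05, at least 64 dyads are needed". Drop-out of 15% brings this to 75, or 25 per country, and the groups are set out as "In total 75 patient-carer dyads who will be offered the MCSP and 75 patient-carer dyads usual care". No ICC or design effect appears. The design is a "controlled trial (pre-test and post-test control group design) with measurements at Month 0 and Month 7", and random assignment is not mentioned. The same section plans evaluation both within each country and overall.

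**Outcome model** (Analysis, Evaluation of effectiveness and cost-effectiveness (question 4a)). ANCOVA is run "on the posttest measurements including the baseline measurements as covariates in the analysis". Other covariates enter if they differ between groups at baseline and correlate with an outcome. Neither country nor centre is named.

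**Delivery.** The intervention section describes a social club three days a week and group meetings for carers. The time plan says: "In each participating country the MCSP is adaptively implemented in at least one region, in one meeting center".

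**Expected centre differences** (Discussion). The article foresees that the three centres may meet different barriers, such as staff competencies, that affect the care received. It would describe these and, only where needed, "take these into account in the effect analyses". No term, trigger or method is given. More centres are foreseen if recruitment falls short.

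**The concern.** The article predicts that the centres will differ in ways that affect care, yet its power statement assumes that all dyads are independent, and its model has no term for country or centre. Two separate consequences follow.

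1. **Country.** Differences between Italy, Poland and the United Kingdom in outcome level, so far as the baseline score does not absorb them, stay in the residual. The covariate rule looks for group differences, and a country recruited 25 to 25 shows none. If recruitment departs from that target in a study that mentions no randomisation, country becomes a possible confounder, and whether it enters the model would depend on a baseline test.
2. **Centre.** Dyads in one meeting centre share staff, a locally adapted programme and a group. If centres are seen as a sample of possible centres, the MCSP arm carries less information than its number of dyads suggests.

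At stake is how far the pooled result reaches. The country-specific comparisons are too small to carry the conclusion (see the working), so the pooled analysis has to.

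**Working it through.** **Inputs from the article:** d = 0.5, power 0.80, alpha 0.05, 64 evaluable dyads, 15% drop-out, 75 per group, 25 per country per group, one centre in each of three countries. **Assumed, because the article gives none:** ICC 0.01 to 0.10 in the MCSP arm only; baseline-outcome correlation r = 0 or 0.5.

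**1. The plan's own figure.** A two-sided two-sample t-test at d = 0.5 needs 63.8, so 64 per group, with power 0.801. Read as a total (32 per group), 64 would give power 0.50, so it is per group. Drop-out: 64/0.85 = 75.3, and 75 × 0.85 = 63.75, so 75 is close enough. The figures reproduce under independent dyads.

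**2. Centre clustering in the MCSP arm.**
- Dyads per centre: m = 64/3 = 21.3
- Design effect: DE = 1 + (m − 1) × ICC
- Inflation of the variance of the group difference: I = (DE + 1)/2
- Real error of the independence-based test: 2(1 − Φ(1.96/√I))
- Power with the correct standard error: Φ(0.5/SE − 1.96), with SE = √(I × (1 − r²) × 2/64)
- Allowance for three centres: Satterthwaite df = (A + B)²/(A²/2 + B²/63), with A = (1 − r²) × DE/64 and B = (1 − r²)/64; power is then taken from the noncentral t.

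Example, ICC 0.05: DE = 1 + 20.33 × 0.05 = 2.02; I = 1.51; error = 2(1 − Φ(1.96/1.228)) = 0.111; SE = √(1.51 × 2/64) = 0.217; power = Φ(0.5/0.217 − 1.96) = 0.63; df = 4.4.

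| ICC | DE | Real error | Power, r = 0 | Power, r = 0.5 | With few df, r = 0 | With few df, r = 0.5 |
|---|---|---|---|---|---|---|
| 0 | 1.00 | 0.050 | 0.81 | 0.90 | 0.70 | 0.81 |
| 0.01 | 1.20 | 0.062 | 0.77 | 0.88 | 0.63 | 0.75 |
| 0.02 | 1.41 | 0.074 | 0.73 | 0.85 | 0.57 | 0.69 |
| 0.05 | 2.02 | 0.111 | 0.63 | 0.76 | 0.44 | 0.55 |
| 0.10 | 3.03 | 0.168 | 0.51 | 0.63 | 0.31 | 0.39 |

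For r = 0.5 the ICC refers to the baseline-adjusted residual.

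**3. Country left out, no centre effect.** The stated ANCOVA was simulated with 21 per arm per country, r = 0.5 and an assumed between-country SD of 0.5 (in within-country outcome SDs) that baseline does not absorb. Without a country term, error is 3.5% and power at d = 0.5 is 0.83. With it, power is 0.89. Omission costs power and does not inflate error.

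**4. Whether country terms repair clustering.** In the same simulation at ICC 0.05, error with country in the model is 10.7% to 11.6%. Adding group-by-country and averaging the country effects leaves it at about 11% to 12%. Neither term helps if centres are treated as random.

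**5. Inference limited to these centres.** With fixed centre deviations of SD about 0.22 that average to zero, the stated ANCOVA has 4.9% error and 0.88 power with no country differences, and 3.6% and 0.86 with a between-country SD of 0.5. For this narrower effect the error rate is not inflated.

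**6. Country-specific comparisons.** An unadjusted t-test at d = 0.5 has power 0.41 with 25 per arm and 0.35 with 21.

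**7. Adjusting for implementation differences.** With one centre per country, features of a centre's implementation exist only in the MCSP arm and vary only by country. They coincide with the group-by-country contrast, so no covariate can separate the two.

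**The case against.** The strongest case on the other side has five parts.

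- **The ICC is not in the article.** At zero both stated figures hold, and with r = 0.5 power stays above 0.80 up to an ICC of 0.02 on the normal approximation. This stands. A reader might infer that 0.80 power and 5% error are simply not delivered. The article does not support that; the failure is conditional.
- **Omitting country is not an error-rate problem.** This also stands. A reader might infer that the missing country term inflates false positives, but under the planned balance it does the opposite. Baseline adjustment on the same scale also absorbs part of any country shift.
- **Limiting inference to these centres removes the 6% to 17%.** Correct, and it is why the two claims must be kept apart. The remedy narrows the conclusion; it does not rescue a wider one. The article nowhere states a formal statistical inference to Europe as a whole, so that reading should not be attributed to it.
- **Country is not ignored.** Evaluation within each country as well as overall is planned, and more centres may open. Both are true. But no pooled model follows from this, and the covariate rule could bring country in only if recruitment became unbalanced.
- **A condensed article leaves model terms to a fuller document.** This carries weight for standard-error methods. It does not cover what the article itself fixes: the sample-size basis, a covariate rule that passes over country, and an open-ended adjustment that cannot be carried out with one centre per country.

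**Conclusion.** The point holds in two parts of different weight. First, the pooled ANCOVA should contain country by design: leaving it out costs some precision (0.83 against 0.89 power in the simulated case) and leaves confounding open if recruitment is uneven, but it does not raise type I error. Second, the 0.80 and 5% apply to the effect in the participating centres, or to a wider effect only if between-centre variance is nil. For wider generalisation, an assumed ICC of 0.01 to 0.10 in the MCSP arm gives error of about 6% to 17%. Power is then 0.77 to 0.51, or 0.88 to 0.63 with r = 0.5. Counting the degrees of freedom from three centres, it falls to 0.63 to 0.31, or 0.75 to 0.39. These ranges rest on the assumed ICC and r, equal centre sizes and clustering in one arm only. A reader might expect a country term to settle both parts; it settles only the first.

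**What to change.** - Include country as a prespecified fixed effect in every pooled ANCOVA, whatever the baseline tests show.
- Add group-by-country, and report the average of the three country effects beside the country-specific effects already planned. If further centres open, add centre within country.
- State that inference is conditional on the participating centres.
- Say that the 0.80 and 5% refer to that conditional effect or assume no between-centre variance, and give the range above for anyone generalising further.
- Replace the conditional adjustment in the Discussion with a descriptive comparison of country-specific effects and process findings.

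The cost is about four degrees of freedom (two for country, two for group-by-country) and a narrower, less favourable statement of what the trial can show. No additional dyads are needed.

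### With no random allocation described, covariates beyond the baseline outcome enter the ANCOVA only if they differ between groups at baseline, so moderate confounding can be left unadjusted

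*Protocol article*

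**What the plan says.** The Phase 2 section of the protocol article sets up the effectiveness comparison "by means of a controlled trial (pre-test and post-test control group design) with measurements at Month 0 and Month 7", with usual care as comparator. The group sizes are: "In total 75 patient-carer dyads who will be offered the MCSP and 75 patient-carer dyads usual care". Random allocation is not described anywhere in the article.

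The same section plans a comparability check, per country and overall, on "severity of the dementia and degree of assistance/care needed by the patient, and the sense of competence of the caregiver". It does not say that the model will adjust for these three characteristics.

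The analysis section on effectiveness and cost-effectiveness (question 4a) then fixes three things:

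- For baseline characteristics, "differences between the groups will be tested (two-sided, alpha 0.05) by t-tests and Chi2 tests".
- Each outcome is analysed by ANCOVA on the post-test value, always with the baseline value as a covariate.
- Potential confounders are added to that model, defined as "characteristics that differ between the groups at baseline and are correlated with one or more outcome measures".

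**The concern.** Without randomisation, systematic differences between the people who use MCSP and those who use usual care are the main threat to the comparison. The article itself records who referred participants to each type of care and lets sites set their own access criteria for MCSP. Covariate adjustment is the only analytic protection it describes.

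The rule makes that protection depend on a baseline test. A non-significant test at this sample size does not show that a characteristic is balanced, and a moderate imbalance in a prognostic characteristic is enough to shift the estimate. Several small shifts in the same direction add up. The covariate set is also chosen from the trial's own data, and the reported standard errors take no account of that choice.

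This is a rule that the article states, so it is not a detail left to a document that is not shown.

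**Working it through.** **Inputs from the article.** 75 dyads per group, 25 per group per country; baseline tests two-sided at 0.05; design effect d = 0.5, power 0.80, drop-out 15% (Phase 2 section).

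**The plan's own figure.** The article states "a power of 0.80 and alpha 0.05, at least 64 dyads are needed". A two-sided two-sample t-test with d = 0.5 has power 0.8015 at 64 per group and 0.795 at 63, so 64 is right when read as a per-group number. For drop-out, 64/0.85 = 75.3, and 75 × 0.85 = 63.75. The figures of 75 recruited and about 64 analysed per group are reproduced to within rounding.

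**Chance that a true imbalance is detected.** For a standardised difference d and n per group, the test statistic follows a noncentral t with 2n − 2 degrees of freedom and noncentrality d × √(n/2). The imbalance counts as detected if the statistic exceeds the two-sided 5% critical value.

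Example: d = 0.3, n = 75. Noncentrality = 0.3 × √37.5 = 1.84; critical value 1.976 on 148 df; probability 0.446.

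| True imbalance (SD) | 75 per group | 25 per group (one country) |
|---|---|---|
| 0.2 | 23% | 11% |
| 0.3 | 45% | 18% |
| 0.4 | 68% | 28% |
| 0.5 | 86% | 41% |

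The probability reaches 50% at 0.32 SD with 75 per group and at 0.57 SD with 25 per group. The second condition, correlation with an outcome, lowers retention a little further.

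**Consequence for the treatment effect.** The article gives no expected imbalance and no number or strength of confounders, so these are assumptions: no true effect; 64 per group analysed; coefficient 0.5 of the baseline outcome on the post-test; independent confounders, all imbalanced in the same direction, each with an effect of 0.3 SD. With no extra adjustment the bias is (number of confounders) × imbalance × effect; for three at 0.3 SD it is 3 × 0.3 × 0.3 = 0.27 SD. Simulation, with both conditions of the rule applied, gives:

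| Confounders | Rule: bias | Rule: type I error | Always adjust: bias | Always adjust: type I error | No extra adjustment: bias |
|---|---|---|---|---|---|
| One at 0.3 SD | 0.03–0.04 SD | about 5% | 0.00 | about 5% | 0.09 SD |
| Three at 0.2 SD | 0.10 SD | about 9% | 0.00 | about 5% | 0.18 SD |
| Three at 0.3 SD | 0.10–0.11 SD | 10–11% | 0.00 | about 5% | 0.27 SD |
| Three at 0.5 SD | about 0.05 SD | about 7% | 0.00 | about 5% | 0.45 SD |

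The ranges cover running the baseline test on the 75 recruited or on the 64 analysed per group. With three confounders at 0.3 SD, always adjusting also gives a smaller SD of the estimate (0.128 against 0.144).

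**The case against.** A reader might infer that the ANCOVA adjusts for nothing but significant imbalances. It does not: the baseline value of each outcome is always in the model and removes part of the confounding. Carer competence, measured by the SSCQ, is itself an outcome, so it is always adjusted for in that one analysis.

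A reader might also infer that real confounders are generally dropped more often than kept. That reverses above about 0.32 SD with 75 per group, and the article gives no expected imbalance on which to base a general statement.

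Nor does it follow that the estimate must be materially biased. The larger figures need several confounders acting in the same direction. With one, the type I error stays near 5%. With three imbalanced by 0.3 SD, each with an effect of 0.15 SD and a correlation of 0.3 with the baseline outcome, the bias is about 0.04 SD and the type I error 5.5%. Such correlation is plausible, because severity and care need are likely to be related to baseline behaviour and mood. The rule also does useful work: for three confounders at 0.3 SD it cuts the bias from 0.27 to about 0.11 SD.

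Two further points are fair. The sentence with the rule does not repeat the 0.05 level, so significance is inferred from the tests described just before it; if something else is meant, no cut-off is fixed at all. And the zero bias under fixed adjustment holds by construction, because every simulated confounder is measured and modelled correctly.

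All this limits the size of the problem. It gives no reason to prefer the rule: fixed adjustment had less bias in each scenario above, and the article itself names three characteristics on which it wants the groups to be comparable.

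**Conclusion.** The point holds in limited form. In a comparison with no described randomisation, making confounder adjustment depend on an observed baseline difference is a badly fixed rule. It misses most true imbalances below about 0.32 SD overall, and below about 0.57 SD within a country. Under the stated assumptions the remaining bias runs from about 0.03 to 0.04 SD with no visible inflation of the type I error (one confounder) to about 0.11 SD with a type I error of 9 to 11% (three at 0.2 to 0.3 SD). The upper figure is about one fifth of the design effect (0.11/0.5 = 0.22).

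The detection probabilities rest on the article's own numbers. The bias and error rates rest on the assumed number, strength, direction and independence of the confounders. That the study is not randomised is inferred from the absence of any allocation method. This should be fixed before analysis; it does not invalidate the study.

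**What to change.** Delete the selection rule. State that every ANCOVA adjusts, whatever the baseline tests show, for the baseline value of the outcome, country, GDS stage, degree of assistance needed and baseline SSCQ. Other background items already collected, such as gender, socio-economic status and comorbidity, may be added if they are named before the data are seen. Keep the baseline comparison as a descriptive table.

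Referral source should not be forced into the model: it may nearly determine the group, which would cost precision and overlap. Propensity weighting is not needed to repair this point.

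The change is one of wording and uses data already planned. Beyond the baseline outcome, the set costs about five degrees of freedom (two for country, one each for GDS stage 4 or 5, care need as a score, and SSCQ) out of about 128 dyads (2 × 64). Unmeasured confounding remains under any such adjustment and should be stated as a limitation.
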